### 2.13. Sample Size Calculation

The sample size was estimated based on power analysis using the CARS score. To our knowledge, no previous reports have examined the effects of nutritional interventions on FCR, so there is no reference on which we can base our power calculation.

In our observational study conducted between 2017 and 2018, the mean CARS score of a subset of breast cancer survivors who met the eligibility criteria for this study with a prior history of chemotherapy and CARS score ≥3 was 3.96 (SD ± 0.67). Furthermore, in this study, the intervention will be considered clinically significant if the mean CARS score at week 12 in the intervention group is 1 point lower than the mean CARS score at week 12 in the control group. The CARS score ranges from 1 (not worried at all) to 6 (always very worried). In the opinion of breast surgery specialists (TK and AM), a 1-point decrease in this score from 4 (somewhat worried) to 3 (slightly worried) is clinically significant.

Thus, based on the above hypothesis and the results of our previous study, the mean difference in CARS scores was estimated to be 1.0 ± 0.67 (SD) between the Bifidobacterium plus perilla oil group and the control group and between the Bifidobacterium and the control groups at 12 weeks after random allocation. To detect the difference between the two groups, using unpaired *t*-tests with a one-sided alpha of 2.5% and power of 90%, the calculation showed that 11 participants per group would be required in the analysis population. This was calculated using G*Power software (ver.3.1.9.4). Assuming 4 dropouts per group, 15 participants will be enrolled per group (45 in total).

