### 2.14. Statistical Methods

This study is a phase II trial primarily focused on the effects of Bifidobacterium and perilla oil when taken properly. Therefore, the main analysis will be performed in a per protocol set (PPS), which is defined as participants who complete the final post-intervention primary outcome assessment and complete the protocol-specified interventions. Completion of the protocol-specified interventions is defined as completion of least 4 of the 12 weeks of Bifidobacterium and perilla oil administration; these participants will be considered to have completed the protocol-specified interventions based on a meta-analysis of probiotic interventions for anxiety symptoms where the minimum treatment period in studies demonstrating efficacy was 4 weeks [45].

In the secondary analysis, analysis will be performed on all randomized cases based on the intention-to-treat (ITT) principle, and discrepancies in the analysis using the PPS will also be examined. Regarding patient background, summary statistics (mean, standard deviation, and frequency) will be calculated based on the characteristics of the items, and the presence or absence of bias in the three baseline groups in each item will be evaluated based on analysis of variance or the chi-squared test.

The objective of the primary analysis of this study is to collect data to inform a main confirmatory clinical trial (phase III). Regarding the primary outcome, the primary hypothesis is that the mean CARS scores of the intervention groups (Bifidobacterium alone or Bifidobacterium plus perilla oil) at week 12 will be significantly lower than those of the control group. The intervention will be considered effective if the null hypothesis is rejected. The difference in the mean CARS score at 12 weeks after random allocation between the intervention groups and the control group will be analyzed using the unpaired t-test. In the primary analysis, we will not compare the effects between the two intervention groups. Missing values or modeling will not be imputed for primary analysis. Sensitivity analyses will be performed for the primary outcome after imputing missing data using the multiple imputation method.

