The following secondary and sensitivity analyses will be performed for additional discussion of the primary analysis, which will determine the need for further studies. These analyses will be conducted after the primary analysis is completed. For all continuous outcomes (CARS, PHQ-9, IBS-SI, and gut microbiome composition), differences in the scores at 12 weeks and changes between baseline and 12 weeks will be examined using non-paired t-tests and mixed-effect models for repeated measures analysis using repeated timepoints and age, disease duration, and hospital as covariates. For dichotomous or dichotomized categorical outcomes such as ARs and proportion of participants with a moderate or high level of FCR at 12 weeks, relative risk will be calculated. Chi-squared and Fisher’s exact tests will be used for statistical significance testing. The aforementioned analyses will be performed between the combined intervention group (those treated with Bifidobacterium alone and those treated with Bifidobacterium plus perilla oil; *n* = 30) and the control group (*n* = 15). The purpose of this analysis is to increase the power of the hypothesis test to examine whether Bifidobacterium intervention is effective against FCR. This is a supplemental analysis to reinforce the arguments of the primary analysis. Furthermore, to explore the association of changes in symptoms with the gut microbiome and PUFAs, we will perform correlation analyses.

This study will not include an interim analysis. If either of the intervention groups (Bifidobacterium alone and Bifidobacterium plus perilla oil) are inferior to the usual treatment group (control group), it is not a matter of concern whether it is statistically significant or not, so the test will be one-sided. The significance level of the entire test is 2.5% for one side. While this decision might lead to errors in multiple tests, this will be the first study of nutritional intervention for FCR. Therefore, we consider the avoidance of beta errors to be preferable over alpha errors. However, 95% confidence intervals will be presented for differences among groups.

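### The 2.5% one-sided level given for the entire test is the level of each of two primary comparisons; across both it is about 4.5% if neither regimen works

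*Protocol article*

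**What the plan says.** Four statements in the protocol article bear on the error rate.

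- **Overall level (2.14, last paragraph):** "The significance level of the entire test is 2.5% for one side".
- **Level used for sizing (2.13):** the calculation was done "using unpaired *t*-tests with a one-sided alpha of 2.5% and power of 90" percent. The assumed difference of 1.0 (SD 0.67) applies "between the Bifidobacterium plus perilla oil group and the control group and between the Bifidobacterium and the control groups", so there are two primary comparisons and the control group serves in both.
- **Hypothesis and success rule (2.14):** relative to control, the prediction reads "the mean CARS scores of the intervention groups (Bifidobacterium alone or Bifidobacterium plus perilla oil) at week 12 will be significantly lower". The success rule is: "The intervention will be considered effective if the null hypothesis is rejected". The section sets no order for the two tests, no division of alpha and no requirement that both reject.
- **Multiplicity (2.14, directly after the overall level):** "While this decision might lead to errors in multiple tests" is conceded. The reasons given are that this is the first nutritional trial for fear of recurrence and that avoiding beta errors is preferred to avoiding alpha errors. 95% confidence intervals are promised. No figure is given for the resulting overall error rate.

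**The concern.** A level attached to the entire test reads as the probability of a false positive claim across the whole primary analysis. Two tests run at 2.5% each without adjustment do not have that property. The only overall error rate that the protocol states is therefore one the design does not deliver. The figure could pass unchanged into the results paper, where a reader would judge a single positive regimen against 2.5% although the pair of tests carries a larger risk.

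**Working it through.** **Inputs.** From 2.13: difference 1.0, SD 0.67, one-sided alpha 2.5%, power 90%, 11 analysed and 15 enrolled per group. From 2.1: 1:1:1 allocation. From 2.14: unpaired t-tests of each intervention group against control.

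**Step 1: reproduce the planned sample size and see which alpha it uses.** The power of an unpaired t-test with n per group comes from the noncentral t distribution with 2n − 2 degrees of freedom and noncentrality (1.0/0.67) × √(n/2). At n = 11 this is 1.4925 × 2.3452 = 3.50, with 20 degrees of freedom.

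| One-sided alpha per comparison | n per group | Power |
|---|---|---|
| 2.5% | 10 | 88.4% |
| 2.5% | 11 | 91.4% |
| 1.25% (half of 2.5%) | 11 | 85.0% |
| 1.25% | 12 | 88.5% |
| 1.25% | 13 | 91.3% |

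The stated 11 per group reproduces with the full 2.5% on each comparison. If 2.5% had been shared equally between the two, 13 would have been needed. Enrolment also agrees: 11 + 4 = 15 per group, 3 × 15 = 45.

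**Step 2: correlation of the two tests.** Both contrasts subtract an intervention mean from the same control mean. With equal group sizes and a common variance σ², each contrast has variance 2σ²/n and their covariance is σ²/n, so the correlation is (σ²/n)/(2σ²/n) = 0.5.

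**Step 3: overall level when both regimens are ineffective.**

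P(at least one rejection) = 1 − P(Z₁ < 1.96, Z₂ < 1.96) with correlation 0.5 = 1 − 0.9546 = 0.0454.

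Equivalently, 0.025 + 0.025 − P(both reject) = 0.050 − 0.0046 = 0.0454. The ratio to the stated level is 0.0454/0.025 = 1.8.

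**Step 4: small-sample check.** Two million simulated trials with three identical arms and unpaired t-tests gave 4.53% at n = 11 and 4.57% at n = 15. Independent tests would give 1 − 0.975² = 4.94%, so the shared control lowers the figure only slightly.

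**Step 5: does a both-must-win reading rescue the statement?** Under the planning assumptions with 11 per group, the simulated probability that both comparisons reject is 85.5%. That is below the planned 90%, so such a reading would not fit 2.13, and nothing in 2.14 states it.

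**The case against.** The strongest reply is that the protocol does not hide the problem. The sentence after the stated level concedes multiple-testing error and the following one says why it is accepted. On that reading, the entire test is loose wording for the level used throughout, which agrees with 2.13. This largely stands: non-adjustment is a declared and reasoned choice in an exploratory phase II trial whose primary analysis is meant to inform a confirmatory one. It does not rescue the sentence. If 2.5% were the overall level there would be no multiplicity error to concede, and if it is the per-comparison level the sentence should say so.

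A second reply is that the rule that either regimen can succeed is inferred. That is correct: it rests on the word joining the two regimens in the hypothesis, and no explicit at-least-one rule is written. If each regimen is a separate claim, 2.5% is right for each claim, but it is still not the level for the pair.

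A reader might go further in three ways that the documents do not support:

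- **That one false positive sends an ineffective regimen to phase III.** Section 2.14 says that the data will inform a confirmatory trial, and it describes secondary and sensitivity analyses that add to the discussion of the primary result. No passage makes a single rejection sufficient.
- **That 4.5% applies whatever the truth.** It applies when both regimens are ineffective. If one works, the false-positive risk for the other is 2.5%.
- **That the tests must be adjusted or ordered.** The protocol does not rank the two regimens. Testing them in a fixed sequence would lower power for the second comparison from 91.4% to about 85.5%, below the 90% planned for both, and would run against the declared priority of avoiding beta errors.

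**Conclusion.** The point holds as an internal contradiction in a stated error rate. The design spends one-sided 2.5% on each of two primary comparisons; the chance of at least one false positive across them is about 4.5% if neither regimen works, against a stated 2.5%. The calculation assumes equal group sizes, a common variance, unadjusted tests and that a rejection for either regimen counts as a positive finding. It covers only the two primary comparisons, not the pooled-arm or other secondary tests. The decision not to adjust is defensible and is not criticised here. Because the multiplicity is acknowledged in words, the defect lies in the reported figure and not in the choice of analysis.

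**What to change.** Replace the sentence in 2.14 with wording such as: *The significance level is 2.5% one-sided per comparison, with no multiplicity adjustment; for the two primary comparisons together it is about 4.5% if neither regimen works.* Add that a result in which only one of the two comparisons is positive will be interpreted with that overall level in mind. The change costs one or two sentences. It leaves the t-tests, the 11 analysed and 15 enrolled per group, and the stated preference for avoiding beta errors as they are.

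A fixed testing sequence remains an option if the investigators want 2.5% to hold across the two primary comparisons. It is not required, and it would need a revised power statement in 2.13 for the second comparison (about 85.5% with 11 per group).

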### 2.15. Data Management and Monitoring and Auditing

Before the study commences, we will fix the data management process including the case report form (CRF) and will use the EDC system. We have appointed [name]., who is an expert on data management and monitoring, as the Director of Data Management and Monitoring. To ensure that the quality of the data is in accordance with the predetermined protocol, data monitoring will be conducted. Under the supervision of [name], an independent monitor will examine whether the recruitment procedure and data recording adhere to the protocol in the CRF.

This study will be conducted for exploratory research purposes, using commercially available foods with sufficient dietary experience and that pose minimal risk and minor invasiveness. Therefore, data monitoring and auditing by a data monitoring committee are not considered mandatory for this trial. However, in the case that any of the following occur, auditing will be conducted: (1) two serious illnesses for which a causal relationship to the intervention cannot be ruled out; (2) two cases of serious deviation from the protocol; and (3) incidents of critical conflicts of interests.

## 3. Ethics and Dissemination

### 3.1. Ethical Considerations

This study complies with the principles of the Declaration of Helsinki and Clinical Trials Act (No.16 of 14 April 2017) in Japan. This study protocol was approved by the National Center of Neurology and Psychiatry Clinical Research Review Board (CRB 3180006) on 1 Januray 2020 (approval number: CR19-003). This study protocol paper is based on the ver.1.7 protocol (amended approval obtained on 5 February 2020). For any important protocol modifications such as changes to the eligibility criteria, outcomes, or analyses, a formal amendment to the protocol is required.

Written informed consent will be obtained from all participants by the physicians-in-charge and CRC, ensuring sufficient written and verbal explanations. Participants will be informed that they can withdraw from the study at any time without any negative impact totheir care or other services. Each participant will be sequentially assigned a specific number to maintain confidentiality. All study-related information will be stored securely in a locked file cabinet with an anonymously allocated number and restricted access.

### 3.3. Availability of Data and Materials

The results of this study will be disseminated in presentations at academic conferences and publications in peer-reviewed journals. Eligibility for authorship of these publications will adhere to the authorship criteria of the International Committee of Medical Journal Editors (ICMJE). For transparency of trial results and adherence with ICMJE recommendations [46], individual participant data generated in this study will be anonymized and will be shared with researchers for secondary use of the data upon request in accordance with the data sharing policy described in Table 2.

### 3.4. Patient and Public Involvement

Prior to this study, we conducted a systematic review of cancer survivorship guidelines in Japan and clarified the needs of cancer survivors [47]. In the present study, the research question, study design, and outcome measures were determined based on a discussion with participants of previous studies [18,19,48]. The burden imposed by intervention in this RCT will be assessed by the participants themselves and their opinions will be used in the design of the next RCT.

## 4. Discussion

To our knowledge, this will be the first RCT to explore the effects of nutritional intervention on FCR in cancer survivors. This study will also be the first to examine the effects of a combination of probiotic and omega-3 fatty acids (Bifidobacterium and perilla oil) on psychiatric symptoms. This combination is designed based on our previous observational study and growing interest in interaction between the gut microbiome and omega-3 fatty acids.

This study primarily aims to evaluate the preliminary efficacy and effect size of the study treatment to guide future full-scale confirmatory trials of the effects of Bifidobacterium and perilla oil on FCR in cancer survivors. Due to fewer adverse effects than psychotropic drugs, this nutritional intervention should be acceptable for physically vulnerable cancer survivors. It is hard to imagine that these supplementations alone will replace standard psychotropic drugs and psychotherapy in the future. Rather, they will likely be used to complement other treatments. It is also reasonable to consider them as part of behavior change interventions in daily life (physical activity, weight control, smoking cessation, etc.), with the aim of improving well-being in breast cancer survivors.

The advantage of this treatment over other treatments is that it is easy to implement. Bifidobacterium and perilla oil are commercially available from food manufacturers and are readily available. Psychotropic drugs have side effects, including cognitive impairment which can lead to falls, and the problem with psychotherapy is that there are few psychologists in Japan who can provide treatment. If the effects of Bifidobacterium and perilla oil on FCR in cancer survivors are shown to be effective in future full-scale confirmatory trials, their preventive effects will also need to be examined.

The major limitation of this study is the lack of placebo, without which the intervention group is subject to a placebo effect with the attendant risk of overestimating the effect of the intervention versus the control. However, from our experience, cancer survivors are commonly quite reluctant to participate in studies using a placebo. Additionally, people are cautious about the foods they consume, and most would decline anything other than foods that are nutritious, including wasted calories. Thus, we will not use a placebo capsule or sachet in this pilot study. In the next full-scale confirmatory study, we will use a placebo in the control group. Moreover, many foods contain some form of omega-3 or probiotics. Because this study does not control for diet other than supplementation, it is possible that people may unintentionally consume more than the prescribed amount. This may lead to under- or overestimation of the intervention effect. To address this issue, we will measure blood levels of omega-3 fatty acids at baseline and assess dietary habits using a food frequency questionnaire. In addition, after the intervention, changes in dietary habits, supplementation, and history of antibiotic use will be evaluated through an interview, and a secondary analysis will be conducted to account for these effects and to confirm the robustness of the results.

## Figures and Tables

**Figure 1 mps-04-00046-f001:**
[figure not shown]
Flowchart of this trial.

**Table 1 mps-04-00046-t001:** Schedule for the assessments.

		Screening Period		Treatment Period	
	Rater	Pre-Entry Screening	Baseline Assessment ^1^	Random Allocation ^1^	Outcome Assessment ^2^
***Enrolment***					
Screening for eligibility	Physician	×			
Informed consent	CRC/Physician	×			
Registration to EDC	CRC		×		
***Assessment***					
Baseline characteristics of participants	CRC		×		
Blood fatty acid test	CRC		×		
Interstitial flora	CRC		×		×
CARS assessed via interview	CRC/masked rater		×(CRC)		×(masked raters)
PHQ-9	PRO questionnaires		×		×
IBS-SI	PRO questionnaires		×		×
Information about allocated groups	CRC			×	
Adverse reactions	CRC/PRO questionnaires				×
				← As needed throughout protocol →	

^1^ Baseline assessment and random allocation for completion within 3 weeks after registration in this study. ^2^ Outcome assessment will be conducted at 12 weeks from random allocation (allowing for a subsequent 14 days).

**Table 2 mps-04-00046-t002:** Data sharing policy for this study. Abbreviation: IPD, individual participant data.

Data Sharing Policy	
Is IPD available?	Yes
What types of data will be shared?	All anonymized IPD reported in the paper (body text, tables, and figures)
Are there any other documents available?	Protocol paper
How long will the data be available for?	For 5 years after publication of the paper
Who will use the data?	Researchers who have presented plans with appropriate methodologies
What types of analysis will this be used for?	For meta-analyses using IPD
How can the data be accessed?	Interested researchers should send a request for data sharing, along with a synopsis of the secondary analysis plan, to the Principal Investigator (RO) by email ([contact]). The study administrative office will examine the request and, if approved, send a letter of approval for data sharing to the requesting researcher.

## Data Availability

The results of this study will be disseminated in presentations at academic conferences and publications in peer-reviewed journals. For the transparency of trial results and adherence with ICMJE recommendations, individual participant data generated in this study will be anonymized and will be shared with researchers for secondary use of the data upon request in accordance with the data sharing policy.

## Abbreviations

ARs	adverse reactions
ALA	alpha-linolenic acid
CRC	clinical research coordinator
CRF	case report form
CARS	Concerns about Recurrence Scale
EDC	electronic data capture system
FCR	fear of cancer recurrence
FFQ	Food Frequency Questionnaire
IAP	intestinal alkaline phosphatase
ITT	intention-to-treat
ICMJE	International Committee of Medical Journal Editors
IBS	irritable bowel syndrome
IBS-SI	Irritable bowel syndrome severity index
JRCT	Japan Registry of Clinical Trials
NCNP	National Center for Neurology and Psychiatry Hospital
NHO	National Hospital Organization
PHQ-9	Patient Health Questionnaire-9
PPS	per protocol set
PRO	patient-reported outcomes
PUFA	polyunsaturated fatty acid
